# Evaluation of ergonomic and education interventions to reduce occupational sitting in office-based university workers: study protocol for a randomized controlled trial

**DOI:** 10.1186/1745-6215-14-330

**Published:** 2013-10-12

**Keywords:** Sedentary behavior, Musculoskeletal symptoms, Ergonomic, Work posture, Intervention, Behavior change

## Abstract

**Background:**

Prolonged sitting is a specific occupational hazard in office workers. There is growing evidence that prolonged sitting is detrimental to metabolic health. The aim of this study is to determine whether providing office workers with education along with adjustable sit-stand workstations leads to reduction in sitting behavior.

**Methods/Design:**

A randomized control trial (RCT) with three groups (one control group and two intervention groups) will be conducted in an office workplace setting. The education intervention group will receive an education package that encourages reduction in sitting behaviors. The sit-stand desk intervention group will receive the same education package along with an adjustable sit-stand desk. Participants will be included in the study if they are currently employed in a full-time academic or administrative role that involves greater than 15 hours per week or greater than 4 hours per day computer-based work. Baseline data will include participant’s age, gender, weight, height, smoking habit, employment position, level of education, and baseline self-reported leisure time physical activity. The primary outcome is the average daily sedentary time during work hours, measured by an accelerometer. Participant recruitment commenced in March 2013 and will be completed by December 2013.

**Discussion:**

This study will determine whether providing office workers with an adjustable sit-stand desk and individually targeted education, or education alone, is more effective in decreasing sitting behaviors than no intervention.

**Trial registration:**

Australian New Zealand Clinical Trials Registry:
ACTRN12613000366752

## Background

One of the features of modern working life is that jobs are becoming increasingly less active and more sedentary
[1]. Prolonged sitting has been identified as a potentially significant occupational health concern
[2], as higher levels of occupational sitting have been linked to increased prevalence of chronic diseases including coronary heart disease
[3], diabetes
[4], obesity
[5], and breast cancer
[6], as well as increased mortality from all causes
[7]. Risk of musculoskeletal disorders has also been linked to increased exposure to sitting at work
[8]. Given that average working hours have generally increased over the past 32 years
[9], with adults now spending an average of more than 8 hours of their weekday at work
[10], the workplace is a key setting in which to introduce strategies to reduce sitting time and break up periods of prolonged sitting to improve health
[11,12]. Prolonged sitting is of particular concern in certain occupational groups such as office workers
[13]. High rates of sedentary behaviors have been demonstrated in particular groups of office workers including managers, professionals, clerical and administrative workers
[14], public service workers
[8], sales people
[15], and health company workers
[16]. One reason for this might be the shift to the 'paperless office’ and the growing prevalence of computerized work environments
[1]. Observational studies of Australian office workers have demonstrated that up to two-thirds of a working day, or half of an office-worker’s waking hours are spent in sedentary postures
[13,17].

Both education and ergonomic interventions have been trialed in the office workplace environment in an attempt to increase incidental physical activity and reduce sedentary behavior
[18]. Education interventions typically employ behavior change strategies such as goal-setting, self-monitoring, and use of external cues
[19,20]. There is some evidence that strategies such as using pedometers, reducing the use of seated telephone and email time in favor of face to face contact, using a bathroom further away from the office workstation, and having standing and/or walking meetings can increase incidental physical activity at work
[21]. Several studies that have evaluated the effect of education interventions have used an approach based on the transtheoretical (stages of change) model
[22]. This approach matches the education strategy to the individual participant’s readiness to embrace behavioral change.

A number of ergonomic interventions have also been investigated as a means of reducing unhealthy sitting behavior or increasing energy expenditure in office workers. These include walking workstations
[23,24], portal pedal machines
[25], and the use of adjustable sit-stand workstations
[11,26]. Of these, adjustable sit-stand desks
[11,26] show particular promise. The sit-stand desk is an adjustable workstation, which attaches to the worker’s desk allowing adjustment of the height of the computer monitor and keyboard allowing work in a sitting or standing position. This device allows the worker to quickly and easily change working position from sitting to standing enabling workers who are seated for long periods of their workday to have frequent standing breaks. There is some evidence that sit-stand desks are effective. A quasi-experimental study
[11] demonstrated reduction in sitting time between 61 and 137 minutes/day when using one of these devices. However, these results have not been replicated in a randomized controlled trial (RCT). To date there has been no investigation of the effect of targeted education (incorporating behavior change) alone, compared with education plus access to an ergonomic device such as an adjustable sit-stand workstation, on reducing sedentary behavior in office-based workers. Although preliminary studies investigating these interventions applied separately have demonstrated promising results
[11,21,23-26], no single intervention appears to suit all workers. It is also possible that education approaches and ergonomic interventions might have complementary effects.

The aim of this study is to determine whether providing office workers an adjustable sit-stand workstation together with targeted education, or targeted education alone leads to changes in sedentary behavior at work compared with no intervention. A secondary aim is to determine if one intervention is more effective than the other in affecting sedentary time.

## Methods

### Trial design

A RCT with two intervention groups and one control group will be conducted in an office workplace setting. Participants will be recruited from academic and administrative staff of The University of Sydney, Sydney, Australia. The study has been approved by The University of Sydney Human Research Ethics Committee, protocol number 15448. Written informed consent will be obtained from each participant prior to entry into the trial. The trial is registered with the Australian New Zealand Clinical Trials Registry, ACTRN12613000366752. The flow of participants through the trial is demonstrated in Figure 
1.

**Figure 1 F1:**
[figure not shown]
Flow of participants through trial.

### Participants

Sixty participants will be recruited by advertisement from academic and administrative staff at the Faculty of Health Sciences, The University of Sydney. Posters will be placed in staff tearooms and common areas, inviting staff to participate in 'The Healthier Office Study’. The advertisements will contain general information informing participants that we are testing simple occupational health interventions and that participants will be provided with an ergonomic device or advice about improving healthy work practices. The advertisements will not contain specific detail about the interventions in order to keep the participants blinded to the interventions that they do not receive. The study will also be advertised in a short presentation at Faculty staff meetings to improve potential participants’ awareness of the study.

Participants will be included in the study if they are currently employed in a full-time academic or administrative role that involves greater than 15 hours per week or greater than 4 hours per day of computer-based work. The number of hours spent performing desk or computer duties will be determined for the purpose of inclusion in the study by self-report. Participants will be excluded if they have planned leave during the study period, any self-reported chronic illness, any self-reported musculoskeletal condition, or if they have a current worker’s compensation claim.

Data collection will involve the participant completing standardized assessment forms developed for this study. The assessment forms were piloted prior to commencement of the study to check for readability and participant burden. It was established that data collection for each participant involved less than 10 minutes of participant’s time. Missing data will be collected by telephone or email contact with the participant.

### Interventions

Participants will be randomly allocated to one of three study groups.

In the education intervention group, participants will receive an education package based on the 'Happy Body at Work’ program developed by a health promotion expert and physiotherapist ([name]). The education package was specifically designed for the participants in this study in consultation with the program author. It incorporates evidence-based principles of optimal seated posture, advice concerning regular postural change between sitting and standing, and physical activity guidelines for promoting a healthy lifestyle. The education package will be delivered by a researcher ([name]) who has received training in health promotion and program content from [name]. The aims of the education package are to improve the participants’ knowledge and understanding about the detrimental effects of prolonged sitting, and to motivate and engage the participants in behavior change in relation to sitting habits. The contents of the program include a multimedia presentation, a physical activity goal-setting exercise, self-monitoring of breaks from sitting, and self-monitoring of daily step count, as well as visual and auditory reminders about taking breaks from sitting.

In the sit-stand desk intervention group, participants will be provided with a WorkFit-S or WorkFit-A adjustable sit-stand workstation (Ergotron, Saint Paul, MN, USA) for a period of 4 weeks. Participants will receive the same education package as the education intervention group. Participants will also receive training in the use of the workstation by a member of the research team. Participants will set individual goals for the time that they will spend working in a standing position. Participants will be given the general advice to alternate regularly between work in a sitting and standing position, and discouraged from trying to only work in a standing position.

In the control (no intervention) group, participants will receive no information or advice about postural change and no modification to their office desk set-up. Participants in the control group will be offered the advice intervention once they have completed final data collection and they have been discharged from their involvement in the study.

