## Trial status

At the date of manuscript submission participant recruitment had commenced but had not been completed.

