#### Randomization and blinding

Participants will be randomly allocated into one of three study groups. A researcher who is not involved in participant recruitment or data collection will produce a randomly generated sequence for allocating participants to one of the three groups. This will be done prior to commencement of the trial. This researcher will prepare consecutively numbered sealed opaque envelopes that contain the group allocation for each individual participant. The envelope for each participant will be opened after the participant has enrolled in the study and after baseline data is collected. The randomization sequence will contain equal numbers of subjects in each group but will be otherwise unrestricted.

Data collection will take place away from the participants’ office and data collectors will be instructed not to enter the office areas of participants. This will ensure blinding of the data collectors to allocation of participants to the sit-stand desk intervention group. The office set-up in the workplace setting for this trial is predominantly private, single occupier offices with few work centers using open-plan office design. This feature of the study setting will assist with limiting the exposure of participants to the other trial interventions and ensure blinding of the data collectors to treatment allocation.

Participants will be kept naive as to the main aim of the study, that is, reduction of unhealthy sitting behaviors. This is because it is believed by the research team that participants being aware that the primary outcome is to reduce sitting behavior might actually change this behavior. Participants will also be blinded where possible to the intervention groups to which they are not allocated. Knowledge of the other interventions that are being tested, both clearly being interventions designed to reduce sitting behavior, might also impact on the sitting behavior of participants. Participants will therefore be informed that they are participating in a trial of general workplace health interventions and remain blinded to the other intervention groups.

A researcher who is blinded to the participant allocation will perform data entry and analysis.

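### Offering controls the advice as each one finishes, while recruitment in the same Faculty is still open, adds a secondary but avoidable route for contamination and unmasking

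*Protocol article*

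**What the plan says.** - **Timing of the offer.** Interventions states: "Participants in the control group will be offered the advice intervention once they have completed final data collection", and adds the person's discharge from the study as a further condition. The trigger is the individual's completion; nothing in the article ties it to the end of the trial.
- **Recruitment period.** The Abstract states: "Participant recruitment commenced in March 2013 and will be completed by December 2013". Trial status confirms that at submission "participant recruitment had commenced but had not been completed", so enrolment is staggered.
- **Setting.** Under Participants, all 60 are to be "recruited by advertisement from academic and administrative staff at the Faculty of Health Sciences". Advertising uses shared space ("Posters will be placed in staff tearooms and common areas, inviting staff to participate") and Faculty staff meetings.
- **Content.** Under Interventions, the education package aims to teach the harm done by prolonged sitting and to change sitting habits. Anyone who receives it learns what the trial is about.
- **Masking.** Randomization and blinding keeps participants unaware of the main aim and, where possible, of the other arms. The reason given is: "Knowledge of the other interventions that are being tested, both clearly being interventions designed to reduce sitting behavior, might also impact" on how participants sit. The same section says that mainly private offices will help to limit exposure to the other interventions.

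**The concern.** The masking strategy rests on one premise: people who know that sitting is the target may sit less. Details of the interventions are kept out of the advertisements for the same reason. The rule for the control arm then allows that knowledge to be given to discharged controls while colleagues in the same Faculty are still being measured or have not yet enrolled.

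Two effects are possible. A later control who hears the message may reduce sitting during follow-up, which narrows the difference between control and each intervention arm. A later recruit to any arm may have a lower baseline, which leaves less room for change. Both would probably pull the result toward no difference. In a trial with 20 per arm and no formal power calculation, a null result from this cause would be hard to tell from an ineffective intervention.

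The discharged controls contribute no further data, so the trial gains nothing from educating them early.

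**Working it through.** **Plan's own figure.** 3 groups x 20 = 60, which agrees with the stated total. The article gives no alpha, power, effect size or SD, so there is no power figure to reproduce.

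**Inputs from the article**
- 20 controls; 40 participants educated by allocation (Sample size calculations; Interventions).
- Recruitment window: 1 March to 31 December 2013 is 305 days (43.6 weeks, 10.0 months) at the longest; 31 March to 1 December is 245 days (35.0 weeks, 8.0 months) at the shortest.
- A 7-day baseline period, then 4 weeks to follow-up, with a further 7-day accelerometer period at the end of the intervention (Primary outcomes; Secondary outcomes).

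**Assumptions**
- Enrolment is spread evenly over the window.
- Time from enrolment to discharge is 5 to 8 weeks.
- Education by allocation starts 1 week after enrolment.
- Every control accepts the offer. This is an upper bound.

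**Step 1: controls offered the advice before recruitment closes.** Expected number = 20 x (T - w)/T, with T the window and w the time in study, both in weeks.

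| T (weeks) | w = 5 | w = 6 | w = 8 |
|---|---|---|---|
| 35.0 | 17.1 | 16.6 | 15.4 |
| 43.6 | 17.7 | 17.2 | 16.3 |

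So about 15 to 18 of 20.

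**Step 2: who is still to come.** Simulating 60 evenly spread enrolments randomized 20:20:20 under the same assumptions, about 43 to 50 of the 60 enrol after the first control has finished. By definition, the other 19 controls also finish after that point.

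**Step 3: how much this route adds.** Take a participant's own final measurement and count the colleagues already educated.
- *Through the control offer.* By symmetry, half of the other controls have finished earlier: 19/2 = 9.5 for a control and 20/2 = 10 for anyone else. The average is (20 x 9.5 + 40 x 10)/60 = 9.8.
- *By allocation.* The simulation gives 24 to 27.
- *Share through the control offer.* From 9.8/(9.8 + 23.8) = 29% to 9.9/(9.9 + 27.4) = 27%.

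As a check for a control participant alone, the chance that a given educated colleague has already started is p = 1/2 + a/T - a²/(2T²), with a = w - 1. This gives p = 0.59 to 0.68, so 40p = 23.5 to 27.2 educated colleagues. The share is then 9.5/(9.5 + 27.2) = 26% to 9.5/(9.5 + 23.5) = 29%, in line with the simulation.

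**Step 4: after the change.** If the offer waits for the last participant's final data collection, the 9.8 falls to 0. The 24 to 27 educated by allocation are unaffected, so roughly 71 to 73% of the educated pool remains.

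**The case against.** The strongest reply is that this is a minor route. Two-thirds of the sample receive the same education by allocation, in the same Faculty and over the same months, and they too can talk to colleagues. That stands: the control offer supplies the smaller part of the pool, and only at full uptake.

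The article also recognizes exposure and points to mainly private offices. That stands in part. It claims only that the setting helps to limit exposure, and offices do not cover tearooms, common areas or staff meetings.

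Third, each control is protected until that person's own data are complete, and masking to other arms is promised only where possible. So the two sections are in tension rather than in flat contradiction, and the risk is indirect, through contact between colleagues.

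Fourth, the advertisements tell staff that they will receive a device or advice, and the offer at discharge is how controls get it. Delaying it has a cost for them, and recruitment had already begun.

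A reader might go further and put a size on the damage, for instance by taking a share of the 61 to 137 minutes/day quoted in the Background, or by computing lost power. The document does not support either. That range comes from a quasi-experimental study of people using sit-stand desks, whereas discharged controls are offered advice and no desk. No effect of education is quoted, no contamination rate is given, and no alpha, power or SD is stated. Any such figure would also have to be divided between this route and the larger one.

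**Conclusion.** The point holds as a modest design weakness. The timing rule lets about 15 to 18 of 20 controls be offered aim-revealing content before recruitment closes, which the article does not reconcile with its own reason for masking. Any bias is probably toward no difference.

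The route is secondary: at most about 27 to 29% of the educated colleagues around a participant at final measurement. These figures rest on even enrolment, 5 to 8 weeks in the study, an 8 to 10 month window and, for the share, acceptance by every control. The size of any bias cannot be derived from the document.

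It would be tempting to conclude that the rule does spread the intervention, or that later controls will sit less. The document shows only that this could happen: the advice is offered rather than imposed, and how much colleagues discuss it is unknown. Nor would removing this route make the trial free of contamination. The case for change is that the risk is avoidable at little cost, not that it is large.

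**What to change.** Amend Interventions so that controls are offered the advice only after the last participant in the trial has completed final data collection. Because recruitment had already begun, apply this at least to controls who have not yet been offered it, and align the participant information.

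The sample size, arms, outcomes and analysis do not change, and controls still receive the advice. The downside is that the earliest controls wait up to about 8 to 10 months longer for general workplace advice, and that the terms change for some people already enrolled. The change removes only the added route; exposure to colleagues educated by allocation stays as it is.

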## Trial status

At the date of manuscript submission participant recruitment had commenced but had not been completed.

### Outcome measurements

#### Baseline measurements

A researcher who is blinded to subject allocation will record baseline and outcome data. Baseline data will be collected from participants at the initial assessment to obtain a profile of the participant’s demographic, work, and general health characteristics. This profile will include the participant’s age, gender, weight, height, smoking habit, employment position, and level of education. Baseline self-reported leisure time physical activity will also be measured at this point using the Active Australia Questionnaire
[27]. Recall instruments of physical activity such as the Active Australia Questionnaire correlate with actual physical activity measures such as accelerometer data
[28].

#### Primary outcomes

The primary outcomes are the average daily sedentary time during work hours and the average number of breaks per day. These will be measured over a 7-day period immediately prior to randomization and at the completion of the intervention period. Sedentary time will be measured using an accelerometer (ActiGraph GT3XP, ActiGraph, Pensacola, FL, USA) and participants will be required to keep a log of work hours during these measurement periods. Following this period all data will be downloaded and analyzed. The ActiGraph accelerometer is a small, lightweight, plastic device worn around the waist. It measures motion data using three axes. This device is reliable and provides stable measurements of physical activity when compared to other measures of physical activity
[29].

